## Abstract

**Introduction:**

Patellofemoral pain syndrome (PFPS) is a prevalent chronic knee disorder that poses significant clinical challenges due to its high incidence and suboptimal long-term outcomes. Current diagnostic approaches, primarily reliant on static imaging and subjective assessment, fail to capture the underlying dynamic biomechanical dysfunction. To address this gap, this study integrates dynamic radiography with three-dimensional gait analysis to construct a dynamic biomechanical model of the knee joint. We will quantify key parameters such as patellar tracking. The research is designed to achieve three core Objectives: firstly, to quantify dynamic biomechanical parameters in PFPS patients using dynamic DR and gait analysis; secondly, to compare the effects of biomechanically monitored targeted exercise combined with TCM vs. conventional exercise combined with TCM on pain and function; thirdly, to develop a biomechanics-guided clinical rehabilitation protocol for PFPS patients.

**Methods and analysis:**

This single-centre, prospective, interventional cohort study will investigate the effectiveness of a biomechanically monitored targeted exercise protocol combined with Traditional Chinese Medicine (TCM) compared with conventional exercise combined with TCM in patients with patellofemoral pain syndrome (PFPS). We will consecutively recruit 96 eligible patients. Participants will be assigned to either an experimental group or a control group based on their preference after receiving standardized information. The experimental group will receive biomechanical monitoring, targeted exercise, and Traditional Chinese Medicine (TCM), whereas the control group will receive conventional exercise and the same TCM regimen.

Outcomes will be assessed at baseline, 6 weeks, 6 months and 3 years post-intervention. The primary outcome measure will be pain intensity measured using the Visual Analog Scale (VAS). Secondary outcome measures will include: biomechanical parameters; pain (Knee Pain Scale); joint function (Lysholm Knee Scoring Scale); kinetic parameters (mean power and pulling acceleration during stair climbing using the IDEEA system); spatiotemporal gait parameters (walking speed, step frequency, double support time during stair climbing using IDEEA); and quality of life (36-Item Short Form Health Survey).

For statistical analysis, independent samples *t*-tests will be used for between-group comparisons, and linear mixed-effects models will be applied for outcomes measured at multiple time points. To control for expectation bias, patients' treatment expectation scores will be recorded at baseline and adjusted as covariates if significant between-group differences exist. Baseline characteristics will be compared, and any imbalanced variables will be included as covariates in the primary analysis. A two-tailed *P*-value < 0.05 will be considered statistically significant.

**Clinical Trial Registration:**

Chinese Clinical Trial Registration Number: ITMCTR2025002287

## Introduction

1

Patellofemoral pain syndrome (PFPS) is the most prevalent chronic knee disorder among adolescents and adults, characterized primarily by peripatellar or retropatellar pain during patellofemoral joint loading activities (e.g., squatting, stair ambulation, and running) (1–6). Evidence indicates that about 80% of individuals with PFP continue to have pain despite completing rehabilitation programs (7). Patellofemoral pain syndrome represents a major socioeconomic burden, evidenced by musculoskeletal disorder costs of £7.4 billion per year in the UK and over $213 billion in the US (5). Therefore, this disease presents a critical clinical challenge, driven by the convergence of high prevalence, suboptimal long-term outcomes and significant economic costs that highlight the pressing need for objective diagnostic tools.

It has been established in the literature that the diagnosis of patellofemoral pain is challenging, partly due to the absence of a clear gold-standard reference test (8, 9). Within the domain of medical imaging, a key limitation is that static imaging cannot adequately assess dynamic patellar function, as it provides only a snapshot of non-physiologic joint position (10). Consequently, clinical decision-making becomes disconnected from the core pathomechanism, resulting in imprecise diagnosis, non-targeted therapy, and unstable therapeutic outcomes.

To address these challenges, it is imperative to shift the focus toward dynamic biomechanical assessment. This approach directly targets the core issue by quantifying patellofemoral joint function during activity, thereby bridging the critical gap left by conventional subjective evaluation and static imaging.

Research indicates that the etiology of PFPS is multifactorial, with biomechanical factors such as quadriceps weakness constituting a key modifiable risk factor (4). Biomechanical monitoring technologies offer a means to directly quantify the dynamic function of the patellofemoral joint. These techniques enable the objective measurement of kinematic and kinetic parameters during functional activities such as walking, running, stair ascent/descent, and squatting, thereby uncovering the core pathological mechanism of PFPS: dynamic biomechanical dysfunction. Biomechanical monitoring technologies provide critical technical means for the accurate assessment of PFPS. The core techniques primarily include three-dimensional motion capture systems (11, 12), force platforms (13, 14), and surface electromyography (15–17), all of which have been widely applied in relevant research.

Additionally, a review of the literature reveals that the core advantage of dynamic DR over traditional static DR lies in its ability to capture functional and dynamic anatomical information of the knee joint under weight-bearing or motion conditions (18). This enables earlier and more comprehensive detection of pathological changes that manifest only under load or during activity. Consequently, it significantly enhances the diagnostic capability for functional knee disorders, such as patellar tracking abnormalities and early joint space narrowing. Future trends will focus on integrating dynamic DR, gait analysis technology, and imaging data (19). By combining joint motion trajectories, mechanical loading, and three-dimensional imaging parameters, an integrated “imaging manifestation-biomechanical mechanism” database will be established. This will further elucidate the pathophysiological processes of the disease and optimize surgical planning, such as the personalized design of tibial tubercle osteotomy and medial patellofemoral ligament reconstruction.

This study focuses on patellofemoral pain syndrome (PFPS) and aims to integrate dynamic DR and gait analysis technology to construct a dynamic three-dimensional biomechanical model of the knee joint. Current diagnostic approaches, primarily reliant on static imaging and subjective assessment, fail to capture the underlying dynamic biomechanical dysfunction. However, PFPS is intrinsically related to abnormal joint loading during dynamic activities such as stair climbing and squatting. Therefore, to provide a rational basis for individualized rehabilitation, biomechanical monitoring is the key to targeted exercise therapy, as it offers precise information on individual movement patterns and joint loading. This study aims to achieve three core objectives: firstly, to quantify dynamic biomechanical parameters in patients with patellofemoral pain syndrome (PFPS) using dynamic DR and gait analysis; secondly, to compare the effects of biomechanically monitored targeted exercise combined with Traditional Chinese Medicine (TCM) vs. conventional exercise combined with TCM on pain and function in patients with PFPS; thirdly, to develop a biomechanics-guided clinical rehabilitation protocol for patients with PFPS.

## Methods and analysis

2

### Study design

2.1

This study will be prospective, interventional cohort study conducted at a single center.

### Setting

2.2

This study will be conducted at Sichuan Provincial Orthopedics Hospital in China. The hospital holds the distinction of being China's first sports medicine hospital and a leading Grade A Tertiary specialized orthopedic center that integrates traditional Chinese and Western medicine. The study is scheduled to begin in June 2026, with completion of the initial phase targeted for December 31, 2026. A planned three-year follow-up period for all participants will commence thereafter. Follow-up will be divided into short-term and mid- to long-term assessments. Re-examination and follow-up will be conducted at 6 weeks, 6 months, and 3 years post-intervention.

### Study population

2.3

#### Recruitment

2.3.1

Prospective participants will be identified and recruited from the outpatient clinics of the Sichuan Provincial Orthopedics Hospital. The target enrollment is 96 patients with a diagnosis of patellofemoral pain syndrome (PFPS).

### Eligibility criteria

2.4

#### Inclusion criteria

2.4.1

To be eligible, individuals must (1) be 40 to 60 years of age; The age range of 40–60 years was selected based on a 10-year review of hospital medical records showing that PFPS patients in our setting are predominantly concentrated in this age group. (2) fulfill the clinical diagnostic criteria for patellofemoral pain syndrome (PFPS), including anterior knee pain exacerbated by functional activities (e.g., stair negotiation, squatting), with imaging (x-ray or MRI) confirming no other knee pathologies; and (3) provide written informed consent.

#### Exclusion criteria

2.4.2

Individuals will be excluded if they have (1) significant systemic disease (e.g., cardiovascular, pulmonary, hepatic, renal, or psychiatric) that could confound assessment or outcomes; (2) concomitant major knee joint pathology such as fractures, ligamentous ruptures, rheumatoid arthritis, or gouty arthritis; or (3) undergone any recent surgical procedure or targeted therapy for the patellofemoral joint. (4) radiographic evidence of knee osteoarthritis with Kellgren-Lawrence grade≥2.

### Group allocation and intervention

2.5

Patients will be assigned to either the experimental group or the control group based on their preference after receiving standardized information about both interventions. Specifically, the experimental group will receive biomechanical monitoring, targeted exercise, and Traditional Chinese Medicine (TCM), whereas the control group will receive conventional exercise and the same TCM regimen as the experimental group.

### Sample size

2.6

The sample size for this study was determined through an *a priori* power analysis based on a two-independent-sample means comparison, aimed at detecting differences in the change scores (pre- to post-intervention) of the primary continuous outcome (VAS) between the two groups. Based on previous studies or pilot data, we assumed a mean difference of *δ* = 1.1*σ* between the groups, with an estimated population standard deviation of *σ* = 2.0. The significance level was set at *α* = 0.05 (two-tailed) and the statistical power (1–*β*) at 0.95. Using the corresponding formula (1), a sample size of 43 participants per group was calculated, resulting in a total of 86 participants.$$n_{1}=n_{2}=2{\left(\frac{z_{\alpha /2}+z_{\beta }}{\delta /\sigma }\right)}^{2}$$

To account for potential loss to follow-up or dropouts and to ensure reliable between-group comparisons and data analysis in a real-world setting, the sample size was increased by approximately 10%. Thus, a total of *n* = 96 participants with patellofemoral pain syndrome are planned to be recruited, with *n* = 48 in each group. All eligible patients will be consecutively assessed for eligibility during the study period and assigned to the corresponding intervention group.

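### The printed sample-size formula and inputs give 22 per group, not the stated 43, so the stated effect, power and n cannot all be right

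*Protocol article*

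**What the plan says.** Section 2.6 (Sample size) of the protocol article describes a comparison of two independent means, "aimed at detecting differences in the change scores (pre- to post-intervention) of the primary continuous outcome (VAS) between the two groups". The inputs are all given there. For the effect, "we assumed a mean difference of *δ* = 1.1*σ* between the groups", and for the spread, "with an estimated population standard deviation of *σ* = 2.0". The test is two-tailed at α = 0.05, with "the statistical power (1–*β*) at 0.95".

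The printed formula has n₁ = n₂ on its left side, so its result is the size of one group. From it the section reports that "a sample size of 43 participants per group was calculated, resulting in a total of 86 participants". An allowance of about 10% for dropout then takes the total to 96, planned as 48 per group. No other section gives a different effect, SD, power or formula.

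**The concern.** A reader who puts the printed inputs into the printed formula gets about half of the stated per-group size. The formula, its inputs and its result stand together in one paragraph and disagree, so a fuller protocol or a separate analysis plan could not make this paragraph correct.

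At stake is what the trial was sized to detect. The paragraph tells the reader that 43 evaluable patients per group give 95% power for 1.1σ, which is 2.2 VAS points at σ = 2.0. That statement is untrue whichever input is wrong. The direction of the error also matters: depending on what was meant by the difference, the trial is either well above its power target or well below it.

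**Working it through.** **Inputs, all from section 2.6.** δ = 1.1σ, so δ/σ = 1.1; σ = 2.0; two-sided α = 0.05, so z = 1.960; power 0.95, so z = 1.645. The sum of the two z values is 3.6048.

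**Attempt to reproduce the plan's figure.** Printed formula: n per group = 2[(z_α/2 + z_β)/(δ/σ)]².

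- 2 × (3.6048/1.1)² = 21.48, rounded up to 22 per group, 44 in total.
- Exact t test (noncentral t): power is 94.6% at 22 per group and 95.4% at 23, so 23 per group and 46 in total.

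The stated 43 per group and 86 in total are not reproduced.

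**Variants of the inputs.** Each change is made alone, with the rest as printed.

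| Change | n per group |
|---|---|
| One-sided α | 18 |
| Power 0.90 | 18 |
| Power 0.80 | 13 |
| Rank test, relative efficiency 0.955 | 23 |
| Rank test, relative efficiency 0.864 | 25 |
| α divided by 3 (three follow-up times) | 27 |

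None reaches 43.

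**Dropout step.** 86/0.9 = 95.6, so 96, or 48 per group. This step is sound, so the error lies before it.

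**Routes that do give 43 or 86.**

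1. Two-group total for δ = 1.1σ: 2 × 21.48 = 42.96, so 43.
2. δ read as 1.1 VAS points, so δ/σ = 1.1/2.0 = 0.55. The printed formula gives 2 × (3.6048/0.55)² = 85.9, so 86 per group. The article has 86 as the total.
3. δ read as 1.1 VAS points and the factor 2 left out: (3.6048/0.55)² = 42.96, so 43.
4. SD of the change score taken as σ√2, as it would be with uncorrelated pre and post values: 2 × (3.6048 × √2/1.1)² = 42.96, so 43. The article does not state such an SD.

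**Power of the planned sizes (exact t test, SD 2.0).**

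| True difference | 43 per group | 48 per group |
|---|---|---|
| 1.1σ = 2.2 points | 99.9% | 99.96% |
| 1.1 points = 0.55σ | 71% | 76% |

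The normal approximation puts the second row at 72% and 77%.

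**Difference with 95% power at 43 per group.** By the printed formula, 3.6048 × √(2/43) = 0.78σ, or 1.55 points. By the exact t test it is 0.79σ, or about 1.6 points.

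**The case against.** The strongest reply is that, taken literally, the error does no harm. With δ = 1.1σ the plan has about twice the patients that its target requires, and the 6-week comparison in section 3.2.2 has 99.9% power. That is correct for the printed inputs. It does not rescue the paragraph, because the article does not establish that the printed δ is the intended one. Giving σ = 2.0 separately is unnecessary if the effect is already in units of σ, which makes a difference in raw points plausible.

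Three stronger readings are tempting, and the document does not support them.

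- A reader might infer that a two-group total was mislabelled as per group and then doubled. The match with 42.96 is suggestive, but routes 2 to 4 fit the stated numbers too, and nothing in the article decides between them.
- A reader might infer that a null result would be misread as ruling out only differences of 2.2 points or more. What a null result rules out is read from its confidence interval, not from the design difference.
- A reader might add that equal groups are not assured, since "Patients will be assigned to either the experimental group or the control group based on their preference". That is a separate design point. As an assumed illustration, 86 evaluable patients split 69:17 would still have 95% power for 0.99σ, below the printed 1.1σ. On the printed effect, imbalance of that size does not undo the stated power.

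**Conclusion.** The mismatch is certain: the printed formula and inputs give 22 per group (23 by the exact t test), against 43 stated, and 44 in total against 86. Effect, power and n as printed cannot all hold.

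The cause is open, and so is the direction of the consequence. If 1.1σ is meant, 43 per group has 99.9% power for it, or 95% power for about 0.79σ (about 1.6 points). If 1.1 VAS points is meant, the printed formula requires 86 per group, 172 in total, and power falls to about 71% at 43 per group and 76% at 48. A reader might conclude outright that the trial is oversized, or that it is underpowered; neither follows until the sponsor states the intended δ. These figures assume that the SD of 2.0 applies to the change score and that the groups are equal. The article gives the SD without saying whether it belongs to the change or to a single measurement.

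**What to change.** First confirm from the working behind section 2.6 which difference (1.1σ or 1.1 VAS points) and which SD of the change score were used. Then restate the section so that n, power and effect agree, keeping 96 enrolled.

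- If δ = 1.1σ is meant: say that the formula requires 22 per group, and that 43 evaluable per group gives 99.9% power for 1.1σ, or 95% power for about 0.79σ (about 1.6 VAS points at SD 2.0).
- If δ = 1.1 VAS points is meant: correct the effect statement, and say that power is about 71% with 43 per group and 76% with 48, not 95%.
- If another SD of the change score was used: state it, and recompute on that basis.

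The cost is one check of the original calculation and a rewording of section 2.6. Enrolment does not change. Under the second reading, the power claim has to come down.

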### Study groups and interventions

2.7

Eligible participants will be allocated to one of two groups.

### Experimental group

2.8

This group will receive biomechanical monitoring, targeted exercise therapy, and Traditional Chinese Medicine (TCM) treatment.

### Biomechanical monitoring

2.9

The biomechanical monitoring in this study consists of two complementary components: a laboratory-based multi-technology assessment integrating CBCT, dynamic DR, MRI, and gait analysis, and a real-world wearable sensor assessment using the IDEEA system during stair climbing.

### Part 1: Laboratory-based multi-technology assessment

2.10

The system integrates four core technologies: Cone-Beam CT (CBCT) provides high-precision static three-dimensional bone structure; dynamic DR enables continuous imaging capture of knee joint flexion/extension movement; MRI clearly displays the morphology of soft tissues such as cartilage and ligaments; and the gait analysis system simultaneously records motion trajectories and surface electromyography (sEMG) signals, supplementing data from the perspectives of dynamics and muscle activity.

#### Workflow

2.10.1

Subjects undergo the aforementioned examinations while performing standardized motions (e.g., stepping up/down). Dynamic DR, gait analysis, and sEMG recording will be performed synchronously during the same standardized motion. Dynamic DR and gait analysis record the continuous movement process. A brief pause is made at the angle where symptoms are most pronounced to perform CBCT scanning, thereby acquiring precise three-dimensional data of this key posture.

#### Data fusion and modeling

2.10.2

The core of data processing lies in multi-source information fusion. A preliminary skeletal motion model is established based on the dynamic DR image sequence. This model is then registered and corrected using the high-precision static CBCT images to enhance its geometric accuracy. Finally, sEMG data is introduced to validate the biomechanical plausibility of the model's motion. Through iterative optimization, a three-dimensional motion model is ultimately constructed that can authentically reflect the biomechanical characteristics of the patellofemoral joint under dynamic loading. All biomechanical measurements will be performed by the same senior technician, and equipment will be regularly calibrated to ensure reliability.

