## Control group

3

This group will receive conventional exercise and the same TCM regimen as the experimental group. The conventional exercise consists of quadriceps exercise (right side as example): supine position with the left knee flexed to 90° and the left foot placed flat on the bed, while the right leg is extended. The participant contracts the quadriceps and dorsiflexes the ankle, then elevates the right leg until the heel clears the bed surface by 30 cm. The position is held for 10 s, followed by a controlled lowering phase over 10 s (one repetition), with a 5 s rest between repetitions. Ten repetitions constitute one set, and three sets are performed per session with a 1 min rest interval between sets. Frequency: once daily for 6 weeks.

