#### Primary outcome

3.1.1

The primary outcome is pain intensity measured using a 0–10 Visual Analog Scale (VAS), where 0 represents no pain and 10 represents the worst possible pain. The change in VAS score from baseline to each follow-up time point (6 weeks, 6 months, and 3 years) will be used as the primary endpoint.

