#### Secondary outcomes

3.1.2

Secondary outcomes include the following: biomechanical parameters, assessed by changes from baseline in patellar tracking using dynamic radiography and three-dimensional gait analysis; pain, measured by the Knee Pain Scale (KPS) (26); joint function, evaluated by the Lysholm Knee Scoring Scale (27, 28); kinetic parameters measured by the IDEEA system during stair climbing, including mean power (W) and pulling acceleration (g); spatiotemporal gait parameters measured by the IDEEA system during stair climbing, including walking speed (m/s), step frequency (steps/min), and double support time (ms); and quality of life, assessed by the 36-Item Short Form Health Survey (SF-36) (29–31).

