#### Data collection

3.2.1

To ensure data accuracy and integrity, a dedicated research coordinator will be responsible for collecting all assessment data. Standardized Case Report Forms (CRFs) will be designed, and a dedicated electronic database will be established to systematically record patient demographics, treatment details, and all outcome measures.

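### One technician makes every biomechanical measurement with no stated masking, so the patellar tracking outcome is open to reading by arm or visit

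*Protocol article*

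**What the plan says.** Section 2.10.2 (Data fusion and modeling) states that "All biomechanical measurements will be performed by the same senior technician" and that "equipment will be regularly calibrated to ensure reliability". These are the only safeguards given for the measurements.

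Section 2.8 says of the experimental arm: "This group will receive biomechanical monitoring, targeted exercise therapy, and Traditional Chinese Medicine (TCM) treatment". Section 2.9 defines that monitoring as the laboratory assessment (CBCT, dynamic DR, MRI, gait analysis) plus the IDEEA stair test. For controls, Section 3 says: "This group will receive conventional exercise and the same TCM regimen as the experimental group". It lists no monitoring.

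Section 3.1.2 names as a secondary outcome "biomechanical parameters, assessed by changes from baseline in patellar tracking using dynamic radiography and three-dimensional gait analysis".

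The article's one provision against bias in assessment, Section 3.1.3, concerns patients' expectations and the VAS. The article neither requires nor rules out masking of the technician, the coordinator or the analyst.

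**The concern.** The same measurement system serves as part of one arm's intervention and as the source of an outcome compared between arms, and one person operates it for everyone. Patients choose their arm (Section 2.5), so they know it and may mention it during a measurement visit.

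Tracking is not a plain instrument read-out. It comes from a motion model built on the DR sequence, registered to and corrected by CBCT, checked against sEMG for plausibility and refined iteratively. Someone may have to decide when a registration is acceptable. If that decision differs between arms or visits, an apparent change in tracking could arise from the reading. At stake is the between-arm comparison of tracking, and any biomechanical explanation of a clinical benefit that is built on it.

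**Working it through.** **1. The passages side by side**

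| Question | Where | What it gives |
|---|---|---|
| Who measures? | 2.10.2 | One technician, all biomechanical measurements |
| Why one? | 2.10.2 | Reliability |
| Is the measurement part of an intervention? | 2.5, 2.8, 2.9 | Yes, in the experimental arm |
| Is it an outcome? | 3.1.2 | Yes, change in tracking |
| Can operation or reading vary? | 2.10.1, 2.10.2 | Pause angle; registration and iterative fitting |
| Is the reading masked? | nowhere | Not stated either way |

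One reader removes between-reader variance. It does not remove a shift in that reader's own readings related to arm or visit. Calibration corrects the instrument, not the reader. The covariate adjustment in Section 3.2.2 and the expectation score in Section 3.1.3 address confounding and patient expectation, so neither removes a reading error.

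**2. Which shift would bias the comparison**

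The outcome is change from baseline. Let e be the mean reading error in each arm at each visit. The bias in the between-arm difference in change is

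b = (e_exp,follow-up − e_exp,baseline) − (e_con,follow-up − e_con,baseline).

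An error that is constant within an arm over visits cancels. So does a visit error common to both arms, although that one distorts change within each arm. The damaging case is an error that depends on arm and visit together, which is why the files should hide both.

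**3. Which outcomes are exposed**

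- Tracking: yes, through registration and fitting.
- IDEEA parameters: exported by the system's software and averaged over three trials (2.11.2), so there is no comparable reading step.
- VAS: described as patient-reported (3.1.3) and not read by the technician.

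**4. Illustration of size**

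The plan gives no figure for reading bias, so there is nothing to reproduce. The inputs are 43 per group as printed in Section 2.6 (48 per group as recruited), a two-sided 0.05 level (3.2.2), and an assumed b in SD units of the change score.

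SE of the standardised difference = √(2/n) = √(2/43) = 0.216, or √(2/48) = 0.204.

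With no true effect, P(reject) = Φ(b/SE − 1.96) + Φ(−b/SE − 1.96).

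| Assumed b (SD) | b/SE, n = 43 | P(reject), n = 43 | P(reject), n = 48 |
|---|---|---|---|
| 0 | 0 | 5.0% | 5.0% |
| 0.1 | 0.46 | 7.5% | 7.8% |
| 0.2 | 0.93 | 15.3% | 16.5% |
| 0.3 | 1.39 | 28.5% | 31.2% |
| 0.5 | 2.32 | 64.0% | 68.8% |

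The printed 43 does not itself follow from the formula in Section 2.6: 2 × ((1.96 + 1.645)/1.1)² = 21.48, so 22 per group. That is a separate matter and does not bear on this point.

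**The case against.** The strongest reply is that the article never says the technician or the coordinator knows the arm. If both arms attend the same measurement visits, being measured does not reveal the arm, and the full protocol, which is not shown, may provide for masking. If controls were not measured at all, there would be no comparison to bias. This reply stands against any claim that the readings are unmasked as a matter of fact. It does not remove the point. The article fixes who measures and why, gives that person the experimental arm's monitoring as well, and describes nothing that would keep the arm hidden.

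The article also does not say whether registration and fitting are manual or automated. The more they are automated, the smaller the exposure.

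Three stronger readings are tempting and are not supported:

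- **That the first objective is compromised.** Section 1 words it as quantifying parameters in patients. It is descriptive and compares no arms.
- **That all outcomes are affected because one coordinator gathers them.** Section 3.2.1 says only that "a dedicated research coordinator will be responsible for collecting all assessment data". It does not say that this person knows the arm or scores anything.
- **That masking is almost free and complete.** Section 2.10.1 says: "A brief pause is made at the angle where symptoms are most pronounced to perform CBCT scanning". That happens live, and coding files afterwards cannot mask it. Baseline data used to guide exercise would be needed promptly, and visits run to 3 years, so masked reading means delay and some repeat work.

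**Conclusion.** The point holds in a limited form. The plan gives the tracking outcome to one technician whose measurements are also part of the experimental arm's package, and states no masking. Knowledge of the arm is likely but inferred. The plan as written secures consistency and leaves reading by arm or visit uncontrolled.

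The exposure is one secondary outcome. The size of any bias cannot be estimated from the document. The false-positive rates above show sensitivity under assumed shifts and do not predict what will happen. They assume no true effect, a normal approximation, equal groups and a shift that acts on the change score. At the low end (0.1 SD) the inflation is small. The conclusion also assumes that the modelling leaves some room for operator decisions, which the description suggests but does not settle.

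**What to change.** State in the protocol that, for the outcome analysis:

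1. Existing staff other than the technician store the dynamic DR, CBCT and gait files under codes that hide arm and visit, and hold the key.
2. The same technician models and reads the coded files in random order, in batches. For example, one batch could follow the 6-month visits, and one could follow the 3-year visits and include re-coded earlier files, so that late readings do not stand apart.
3. Any unmasked baseline reading used to guide exercise is kept separate and does not enter the outcome analysis.
4. Live acquisition, including the pause for CBCT, is not masked by this step. This should be reported as a limitation.

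This keeps the single-reader consistency that the sponsor wants and needs no second assessor. The cost is file coding, a short procedure note, delayed batch reading, a second reading of the experimental arm's baseline files, and a repeat reading of whichever earlier files go into the final batch. It is best fixed before the June 2026 start given in Section 2.2. Later, readings made with knowledge of the arm could be repaired only by re-reading them.
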